**9. Quality Control and Assurance of the Trial**

(1) Laboratory Quality Control Measures

- Establish standard operating procedures and quality control procedures for experimental observation indicators.
- Laboratory test results must be printed by a computer and the data should be traceable.

(2) Standard Operating Procedures for Main Observation Indicators

Strictly adhere to relevant guidelines, consensus, and standards for each evaluation item, such as the CPET examination mainly refers to the "Adult Cardiopulmonary Exercise Testing Guideline"; Implementation of the Six-Minute Walk Test refers to the AST2002 version guideline.

(3) Pre-trial Clinical Training

Training researchers on the trial protocol before the project starts and ensuring consistency in quantifying symptoms and signs. Researchers must sign a declaration.

(4) Measures to Improve Participant Compliance

- Timely reminders for follow-up visits.
- Waiver of all treatment and assessment costs.
- Providing financial compensation to participants who complete all planned treatments and assessments.

(5) Quality Control and Quality Assurance System

Researchers must fulfill their respective responsibilities and strictly adhere to the clinical trial protocol using standard operating procedures to ensure the implementation of quality control and quality assurance systems in clinical trials.

-----  

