**Moxibustion Group:**

Selection of Acupoints: Bilateral Zusanli, Shenque, Guanyuan points.

Acupoint Location: Following the 2006 National Standard of the People's Republic of China "Names and Locations of Acupoints" (GB/T12346-2006): the ST36 is located at 3 cun (about 10 cm) below the patella, outside of the anterior crest of the tibia. CV8 is located at the navel, and CV4 is 3 cun directly below the CV8.

Moxibustion Operation:

- Patient lies supine, exposing the skin at the selected acupoints, hands placed on either side of the body.

- The practitioner affixes the moxibustion device base using adhesive tape on the selected acupoints.
- Ignite the moxa stick on the moxibustion cylinder.
- Position the moxibustion device cylinder so that its top is level with the bottom of the device base.
- Rotate the moxibustion cylinder to adjust the air outlet size, maintaining a distance of approximately 3cm from the skin; make participants feel comfortably warm without burning pain.
- When the warm feeling diminishes, indicating the moxa stick is burnt out, it can be replaced.
- After 60 minutes of moxibustion, close the air outlet, remove the moxibustion device, and place the extinguished moxa stick in a container with water.
- Check the moxibustion device for damage and store it back in the original packaging for future use.
- Each participant undergoes moxibustion once a day (8:00-12:00 AM or 2:00-5:00 PM), 60 minutes per acupoint, five times a week (with weekends off), 12 weeks (60 sessions) in total.

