**Blank Control Group:**

The blank control group will receive no treatment and will be instructed not to undergo any interventions that might affect cardiorespiratory fitness until the trial is completed. Measurements for the blank control group will follow the designated time points as the Moxibustion and Sham Moxibustion Groups.

-----

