### **(6) Observational Time Points**

- After participants are enrolled, collect basic information (general information, dietary habits, exercise habits, etc.) and baseline measures, including VO2peak, AT, serum CCB, 6MWD, SF-36, and QBSQ;
- After the 4th and 8th weeks of treatment, conduct and record twice interim assessments, including VO2peak, AT, serum CCB, 6MWD, SF-36, and QBSQ;
- At the end of the treatment (12 weeks), collect basic information again (general information, dietary habits, exercise levels, etc.) and outcome indicators, including VO2peak, AT, serum CCB, 6MWD, SF-36, and QBSQ;
- Follow-up until the 24th week, evaluating indicators including VO2peak, AT, 6MWD, SF-36, and QBSQ.

-----

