## 11. Statistical Analysis

### (1) Statistical Analysis Plan and Statistical Software

- Full Analysis Set: Refers to the ideal set of participants as close as possible to the intention-to-treat principle (mainly analyzing all randomized participants). This dataset is derived by excluding participants from all randomized participants in the least and reasonable manner. For missing values of the primary variables, carry-forward estimation will be used, bringing forward the results closest to a single observation of the missing data in the trial, and ensuring consistency between the number of participants evaluated for efficacy at the endpoint and those at the start of the trial.
- Statistical Analysis Contents: Actual number of enrolled participants in three groups, dropout and exclusion cases, demographic and other baseline characteristics, compliance, efficacy analysis, and safety analysis.

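### Compensation depends on completing every treatment as well as every assessment, so in the two 60-session arms the payment for attending outcome visits is tied to adherence, while in the blank arm it is not

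*Protocol*

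**What the plan says.** Section 9(4) of the Protocol names three measures to support compliance: visit reminders, free treatment and testing, and "Providing financial compensation to participants who complete all planned treatments and assessments". The payment condition is joint: treatments and assessments. The Protocol shows no partial or per-visit payment, no attendance tolerance for payment and no rule on make-up sessions.

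The treatment load differs by arm. Section 5 schedules moxibustion "five times a week (with weekends off), 12 weeks (60 sessions) in total", and sets the same number of sessions for sham. For the third arm, "The blank control group will receive no treatment". The assessment load does not differ: "Measurements for the blank control group will follow the designated time points as the Moxibustion and Sham Moxibustion Groups". Section 6(6) places assessments at baseline and weeks 4, 8, 12 and 24, so four follow baseline.

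Two further sections bear on the point. Section 4(4) counts a randomised participant who does not finish treatment or observation as a dropout, but tells researchers to contact such people and obtain whatever assessments they can. Section 11(1) describes a full analysis set close to intention-to-treat and says: "For missing values of the primary variables, carry-forward estimation will be used".

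**The concern.** An intention-to-treat comparison needs outcomes from people who stop or skip treatment as much as from those who adhere. A payment that depends on treatment completion works against this. Once a session is missed and eligibility is gone, the payment no longer gives that participant a reason to attend the remaining exercise tests. Those who miss sessions are likely to differ from the others in tolerability, perceived benefit or health, so any outcomes lost this way would not be missing at random with respect to treatment experience.

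The rule also acts differently by arm. Only the two treated arms can lose payment through a missed session. If outcome attendance follows payment to any degree, missingness in comparisons with the blank arm would be unequal, and earlier values would stand in for later ones more often in the treated arms. The direction of the resulting bias cannot be fixed in advance. Analysis cannot recover a peak oxygen uptake that was never measured, so the matter belongs to trial conduct.

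**Working it through.** **1. The plan's own sample size.** Section 3(2) gives a difference of 2.6, SD 3.0, 5% significance, 90% power, 29 per group, 15% dropout, and 35 per group (105 in all). Section 11(2) makes the test two-sided.
- Normal approximation: 2 × (3.0 × (1.960 + 1.282) / 2.6)² = 27.98, so 28.
- Two-sample t-test version: 28.97, so 29.
- Dropout: 29 / 0.85 = 34.1, so 35; 3 × 35 = 105.

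The stated figures reproduce and are not in dispute. One 15% dropout rate is applied to every arm.

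**2. Ways to lose payment, by arm.**

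| Arm | Sessions | Post-baseline assessments | Can lose payment by missing |
|---|---|---|---|
| Moxibustion | 60 | 4 | a session or an assessment |
| Sham | 60 | 4 | a session or an assessment |
| Blank | 0 | 4 | an assessment |

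**3. Illustration of eligibility loss.** The Protocol gives no expected attendance, so let q be an assumed attendance probability, independent between visits, with no make-up sessions. The chance of missing at least one session is 1 − q^60. Adding the four post-baseline assessments at the same q gives 1 − q^64 in a treated arm and 1 − q^4 in the blank arm.

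| q | Treated: misses ≥1 of 60 sessions | Of 35 | Treated: misses ≥1 of 64 visits | Blank: misses ≥1 of 4 visits |
|---|---|---|---|---|
| 0.999 | 5.8% | 2.0 | 6.2% | 0.4% |
| 0.995 | 26.0% | 9.1 | 27.4% | 2.0% |
| 0.99 | 45.3% | 15.8 | 47.4% | 3.9% |
| 0.98 | 70.2% | 24.6 | 72.6% | 7.8% |

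On sessions alone the blank-arm figure is 0% by design. These are chances of losing eligibility under a literal reading. They are not rates of missing outcomes. How many people without the payment would skip an outcome visit cannot be computed from the document, which gives neither the amount nor any attendance data.

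**4. Is power the issue?** Observed cases only: power = Φ(2.6 / (3.0 × √(1/n₁ + 1/n₂)) − 1.96). Take an assumed 30% loss in a treated arm (n₁ = 24.5).
- 5% loss in the blank arm (n₂ = 33.25): Φ(3.255 − 1.960) = 90.2%.
- 15% loss in the blank arm (n₂ = 29.75): Φ(3.177 − 1.960) = 88.8%.

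Power stays near the planned 90%. What is at stake is bias from unequal missingness, which further recruitment would not cure.

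**The case against.** The strongest reply is that the clause is one bullet in a list and does not say that non-completers receive nothing. Payment terms usually sit in the consent form, whose pages are not available here, and a graded scheme could be described there. Section 6(5) records compliance as a ratio of sessions received to sessions planned, so the Protocol expects some missed sessions. This stands in part. That payment goes to completers alone is the plain reading, not the wording. If the consent form says otherwise, Section 9(4) should say so too.

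A reader might infer that someone who misses a session has no reason left to return. The document does not support that. Reminders, free treatment and testing (Section 9(4)) and the duty to follow up dropouts (Section 4(4)) all remain; only the financial incentive is lost. These measures soften the risk without removing it, since staff would be pursuing people for whom the payment had ceased to be an inducement.

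A completion payment also keeps some people in the trial and attending late visits, so its net effect is unknown. That stands, and it is why the point is put as a risk. The carry-forward rule is a separate analysis matter; it is cited only because it determines what happens to values lost in this way.

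**Conclusion.** The point holds as a minor design weakness. As written, Section 9(4) ties the financial incentive for outcome visits to treatment adherence in two arms and not in the third. This creates a risk of adherence-linked missing outcomes that is structurally unequal against the blank arm.

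Two stronger readings should be resisted. First, the moxibustion-versus-sham comparison is not unequal by construction: both arms have 60 sessions and the same rule, so missingness would differ there only if adherence or tolerability did. Second, the 45% against 0% at an assumed 99% attendance is not a forecast of missing data. It rests on independent attendance, no make-up sessions and a literal reading of the clause, and it measures eligibility alone. Over assumed attendance of 99.9% to 98% it runs from about 6% to 70%. Differential loss of outcomes has not been demonstrated.

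**What to change.** Change Section 9(4), and the consent form if it says the same, so that compensation is an equal amount for each outcome assessment attended, identical in all three arms and payable whether or not treatment was completed. If session attendance is to be supported as well, reimburse it separately, per session attended, so that a missed session never affects payment for an assessment.

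The cost is a wording change in two documents and resubmission to the ethics committee, which Section 12(1) requires for revisions made during the trial. Sample size, interventions and endpoints are untouched. The drawbacks are a slightly weaker incentive to attend every session and some added payments to people who would otherwise receive none. The Protocol text available gives no compensation amount or budget, so the net cost cannot be stated.

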**10. Data Management**

(1) Data Recording

- Research records are the source documents of clinical trial participants and are kept

in the office of the director of the Acupuncture and Moxibustion Department at the hospital.

- Requirements for research record keeping: ① Researchers must write research records concurrently while treating participants to ensure timely, complete, accurate, and truthful data recording. ② Any evidence-based corrections in the research records can only be crossed out, and changes noted by the researcher's signature and date, without erasing or covering the original records. ③ Participants' original test reports are pasted into the research records.

#### (2) Data Reporting

- Research records.

#### (3) Data Monitoring

The Ethics Review Committee of the Second Affiliated Hospital of Nanjing University of Chinese Medicine reviews each research record.

#### (4) Data Verification

- Establish an electronic database using Microsoft Excel software.
- Conduct numerical range and logic checks. In case of any doubts, fill out a query list. Researchers will address the issues listed in the query list. After completing the data verification report, lock the database.
- Relevant files about quality control should be saved, such as original records of data consistency checks, numerical range and logic checks, original records during blind review, and records of queries exchanged among researchers.

-----

## 11. Statistical Analysis

### (1) Statistical Analysis Plan and Statistical Software

- Full Analysis Set: Refers to the ideal set of participants as close as possible to the intention-to-treat principle (mainly analyzing all randomized participants). This dataset is derived by excluding participants from all randomized participants in the least and reasonable manner. For missing values of the primary variables, carry-forward estimation will be used, bringing forward the results closest to a single observation of the missing data in the trial, and ensuring consistency between the number of participants evaluated for efficacy at the endpoint and those at the start of the trial.
- Statistical Analysis Contents: Actual number of enrolled participants in three groups, dropout and exclusion cases, demographic and other baseline characteristics, compliance, efficacy analysis, and safety analysis.

### (2) Statistical Analysis Methods

Summarize the demographic characteristics of each group and baseline variable measurements. The Kolmogorov-Smirnov test will be used for assessing data normality. Continuous data will be represented as the mean  $\pm$  standard deviation for normally

distributed data and median (range) for non-normally distributed data. Paired t-tests or analysis of variance (ANOVA) will be used to assess changes in primary and secondary outcomes before and after intervention. Analysis of variance or Kruskal-Wallis test will be used for pairwise comparison of primary and secondary outcomes among groups. Chi-square or Fisher's exact test will be used for analyzing categorical data. Pearson or Spearman correlation analysis will be used to assess the correlation between variables. Statistical analysis will be conducted using the Windows version of the Social Sciences Statistics Software Package (SPSS) 27.0, with significance set at a two-tailed P-value of  $<0.05$ . Graphical analysis will be performed using GraphPad Prism software (version 9.4.0).

-----

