## **2. Research Objectives**

The primary goal is to apply and promote the clinical protocol of moxibustion for tonifying Qi and Blood, thereby enhancing cardiorespiratory fitness in elderly individuals. The aim is to effectively assist the elderly in maintaining health, improving their quality of life, and contributing to elderly care initiatives. This study intends to observe the variations in primary outcome indicators ( $VO_{2peak}$ , AT value, serum central carbon metabolites, 6MWD, etc.) and adverse events occurring under the intervention of moxibustion. It aims to evaluate its effectiveness and safety.

-----

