## **3. Experimental Design Type, Principles, and Procedure**

(1) Experimental Design Type: Randomized Controlled Trial

(2) Principles of Experimental Design:

Sample Size Calculation:

The sample size was determined based on our prior pilot investigation. A mean difference in  $VO_{2peak}$  of  $2.6 \text{ ml} \cdot \text{kg}^{-1} \cdot \text{min}^{-1}$ , with a standard deviation (SD) of 3.0 was observed between the moxibustion and control groups. The estimation conducted via the website (<https://sample-size.net/sample-size-means/>). Approximately 29 participants each group are needed to detect a clinically significant difference in outcome measures at a 5% significance level and 90% statistical power. Considering an estimated dropout rate of 15%, the final sample size required will be 35 for each group, resulting in 105 participants. To recruit this number of participants, we anticipate a study period of 9 months based on our pilot study.

Randomization: Stratified Random Allocation

Control: The study includes apparently healthy elderly individuals, with no underlying diseases. Based on recognized principles of effectiveness, safety, and comparability,

sham moxibustion and no intervention are chosen as controls.

-----

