##### **(1) Inclusion Criteria:**

- Men or women aged between 60 and 80;
- No cognitive impairment;
- Decreased CRF ( $VO_{2peak} < 20\text{ml}\cdot\text{kg}^{-1}\cdot\text{min}^{-1}$  or  $6\text{MWD} \leq 450$  meters).

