**8. Assessment Criteria for Efficacy and Safety**

(1) Comprehensive Efficacy Assessment Criteria: Statistical differences in the main outcome indicators are used to judge efficacy.

(2) Criteria for Severity of Adverse Events:

- Mild: Tolerable for participants, does not affect treatment, requires no special treatment, and has no impact on participants' recovery.
- Moderate: Difficult for participants to tolerate, requires withdrawal of drugs to stop the trial or special treatment, and has a direct impact on the participants' recovery.
- Severe: Endangers the participants' lives, causes death or disability, requires immediate drug withdrawal, or urgent treatment.

-----  

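### Before-after tests on the primary outcomes stand beside the between-group test with neither named as decisive, so a drift shared by all arms could be counted as efficacy

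*Protocol*

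**What the plan says.** Section 11(2), Statistical Analysis Methods, plans two kinds of inferential test on the same outcomes. The first is before-after: "Paired t-tests or analysis of variance (ANOVA) will be used to assess changes in primary and secondary outcomes before and after intervention". The second, in the following sentence, is between arms: "Analysis of variance or Kruskal-Wallis test will be used for pairwise comparison of primary and secondary outcomes among groups". One threshold serves both, "with significance set at a two-tailed P-value of" below 0.05. The section does not say which test decides, and it does not describe the before-after tests as descriptive or supportive.

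Section 8(1) gives the efficacy criterion in one sentence: "Statistical differences in the main outcome indicators are used to judge efficacy". It does not say whether the differences are between arms or between time points. Section 2 is worded around variation in the outcomes, among them "AT value, serum central carbon metabolites, 6MWD, etc.) and adverse events occurring under the intervention of moxibustion", as the means of evaluating effectiveness. It mentions no comparison.

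The sample size in Section 3 is based on a between-arm contrast in VO2peak: a mean difference of 2.6 ml/kg/min, "with a standard deviation (SD) of 3.0 was observed between the moxibustion and control groups".

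**The concern.** A before-after change within one randomised arm is not an estimate of the treatment effect. It also contains whatever moves all arms alike. The protocol makes two such influences plausible:

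- **Familiarisation.** Section 6(6) repeats the cycle test at baseline and weeks 4, 8 and 12 (and again at week 24), so the week-12 result comes from at least the fourth test.
- **Season.** The Expected Progress timetable puts baseline collection in Q3 2024, the start of intervention in Q4 2024 and its end in Q1 2025.

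The sham and blank arms are there to remove these influences, but they do so only when arms are compared with each other. Finding significance in the moxibustion arm and not in a control arm is not a test of the difference between them. If the efficacy criterion can be met by a before-after P-value, the trial can report efficacy when the arms do not differ.

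**Working it through.** **Step 1. Reproduce the sample size, to confirm which contrast the trial was built on.** Inputs from Section 3: difference 2.6, SD 3.0, two-sided 5%, power 90%, dropout 15%.

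- Normal approximation: n = 2 × [3.0 × (1.960 + 1.282) / 2.6]² = 27.98, so 28 per group.
- Exact t calculation: power is 0.8896 at n = 28 and 0.9003 at n = 29, so 29 per group, as stated.
- Dropout: 29 / 0.85 = 34.1, so 35 per group and 3 × 35 = 105 in total, as stated.

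The figure reproduces as a two-sample comparison between arms.

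**Step 2. Behaviour of the before-after test under shared drift and no treatment effect.** From the protocol: SD 3.0, n = 29 evaluable, two-sided 0.05. Assumed, because the protocol does not give them: a drift of 0.5 or 1.0 ml/kg/min equal in all arms, a baseline-to-week-12 correlation ρ of 0.5 to 0.8, and SD 3.0 applying to VO2peak at each visit.

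- SD of change = 3.0 × √[2(1 − ρ)].
- Noncentrality of the paired t-test = drift / (SD of change / √29), with 28 degrees of freedom.
- Example, ρ = 0.7 and drift 1.0: SD of change = 3.0 × √0.6 = 2.32; noncentrality = 1.0 / (2.32 / 5.385) = 2.32; probability of significance p = 0.609.
- Probability that moxibustion is significant and a given control arm is not, the arms being independent: p(1 − p) = 0.609 × 0.391 = 0.238.

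| ρ | SD of change | Drift 0.5: p | Drift 0.5: p(1 − p) | Drift 1.0: p | Drift 1.0: p(1 − p) |
|---|---|---|---|---|---|
| 0.5 | 3.00 | 14% | 12% | 41% | 24% |
| 0.7 | 2.32 | 20% | 16% | 61% | 24% |
| 0.8 | 1.90 | 28% | 20% | 78% | 17% |

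With no drift, p is 5%. With all 35 per arm, the same settings give 16% to 86% for p and 12% to 25% for p(1 − p). If the SD of 3.0 is that of the change rather than of a single visit, the ρ = 0.5 row applies.

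**Step 3. The between-arm test in the same situation.** A drift common to all arms cancels from any difference between arms. A 20,000-run simulation of a three-arm ANOVA on change, with ρ = 0.7, gave rejection rates of 5.1% (n = 29, drift 1.0), 5.0% (n = 35, drift 1.0) and 4.9% (n = 35, drift 0.5).

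**The case against.** The strongest reply is that a between-group comparison is already planned, in the sentence directly after the before-after tests. In a randomised three-arm trial sized on a between-arm difference, the natural reading of Section 8(1) is a difference between groups. Section 2 is a general statement of aims and not a decision rule. All of this stands. A reader might infer that the control arms go unused, or that any significant result whatever is accepted as efficacy. The protocol says neither. What remains is that Sections 8(1) and 11(2) do not choose between two tests that can disagree.

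A reader might also add regression to the mean, because Section 4(1) requires "Decreased CRF". That needs the screening test to double as the baseline, and the protocol points the other way. Section 6(6) takes baseline measures after enrolment, and the timetable puts preliminary screening in Q4 2023 to Q1 2024 and baseline collection in Q3 2024. In a simulation with a separate baseline (assumed population mean 20 to 24, SD 5, equal correlation of 0.8 to 0.9 between tests), drift was about zero and the paired test rejected about 5% of the time. Entry is also possible on 6MWD alone, which weakens selection on VO2peak. So regression to the mean is not part of the case made here.

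The illustrative percentages depend on an assumed drift. The discordance p(1 − p) cannot exceed 25%, reached at p = 0.5, so values near 25% are a ceiling and not a typical result.

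Finally, a statistical analysis plan may exist and may settle the matter. But the protocol itself fixes both the tests and the efficacy criterion, so such a plan would have to narrow Section 8(1). The ambiguity belongs to the protocol.

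**Conclusion.** The point holds as a defect of specification. The protocol plans before-after and between-group tests on the primary outcomes at one significance level, names neither as decisive, and words its efficacy criterion so that either could satisfy it. A shared drift could then be counted as efficacy; it does not follow that it would be. Under the assumptions in the working, at 29 per arm and with no treatment effect, the before-after test in the moxibustion arm is significant 14% to 78% of the time. The pattern of moxibustion significant and control not occurs about 12% to 24% of the time, against about 5% for a between-arm test. The direction of the problem does not depend on those assumptions, because any common drift raises the first rate above 5% and leaves the last unchanged. The percentages themselves are illustrations only.

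**What to change.** In Section 8(1), state that efficacy is judged only by the difference between arms. In Section 11(2), name the deciding analysis as the between-arm difference in the week-12 outcome adjusted for its baseline value, for example by ANCOVA. State there that within-arm changes are reported descriptively, as mean change with 95% CI, and do not support an efficacy claim.

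The cost is wording only. The data are already collected under Section 6(6). The 29 evaluable and 35 randomised per group stand, because they were derived for a between-arm contrast. Baseline adjustment should need no more than this if the SD of 3.0 is that of the week-12 value, apart from one degree of freedom.

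### Group comparisons are unadjusted although every outcome has a baseline value: the tests are valid, but precision is given up, by an amount that depends on a correlation the protocol does not state

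*Protocol*

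**What the plan says.** Section 11(2) fixes the between-group method: "Analysis of variance or Kruskal-Wallis test will be used for pairwise comparison of primary and secondary outcomes among groups". The same paragraph plans a within-group or change analysis: "Paired t-tests or analysis of variance (ANOVA) will be used to assess changes in primary and secondary outcomes before and after intervention". It also says "The Kolmogorov-Smirnov test will be used for assessing data normality", and links normality explicitly only to the choice of summary statistics (mean and SD, or median and range). It names no covariate and no stratum term. It does not say whether the between-group test is run on final values or on changes.

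Section 6(6) schedules "baseline measures, including VO 2peak , AT, serum CCB, 6MWD, SF-36, and QBSQ". All of these are repeated at weeks 4, 8 and 12, and all except the serum metabolites at week 24. Section 3(2) states "Randomization: Stratified Random Allocation". The Expected Progress timetable repeats that grouping is stratified. Neither place names a factor.

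The sample size in section 3(2) rests on a VO2peak mean difference of 2.6 with SD 3.0 ml/kg/min, "at a 5% significance level and 90% statistical power". This gives 29 per group, 35 after 15% dropout, and 105 in total. Section 8(1) judges efficacy by statistical differences in the main outcomes, so these tests carry the trial's conclusion.

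**The concern.** A baseline measurement of the same variable usually explains part of the follow-up variance. A comparison that leaves it out has a wider confidence interval than the data require, and if final values are compared, chance imbalance at baseline stays in the estimated difference. If allocation is stratified on prognostic factors and the analysis ignores them, standard errors tend to be too large.

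The Kruskal-Wallis alternative has a second cost. The trial is sized to detect a mean difference in ml/kg/min, and a rank test does not estimate one. If that route is taken, the result cannot be set against the 2.6 used in planning.

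This is a stated choice of method, so it is not simply detail left for a statistical analysis plan.

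**Working it through.** **Inputs from the protocol.** Difference 2.6, SD 3.0, two-sided 5%, 90% power, 15% dropout (sections 3(2) and 11(2)).

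**Assumed.** The baseline to follow-up correlation r is not given, so 0.3, 0.5, 0.7 and 0.8 are shown. The SD is taken as equal at baseline and follow-up.

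**1. The plan's own figure.** By normal approximation, n = 2 × (1.960 + 1.282)² × 3.0² / 2.6² = 27.98, so 28 per group. The exact noncentral-t calculation gives 88.96% power at 28 and 90.03% at 29, so 29 per group. Then 29 / 0.85 = 34.1, rounded up to 35, and 3 × 35 = 105. The stated figures reproduce without any adjustment.

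**2. Variance formulas.** With common variance σ²:
- final value: σ²
- change: 2σ²(1 − r)
- baseline-adjusted: σ²(1 − r²)

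Adjustment therefore saves r² of the variance against final values. Against changes the ratio is (1 − r²) / [2(1 − r)] = (1 + r)/2, a saving of (1 − r)/2.

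**3. Results.** The protocol does not say whether SD 3.0 refers to the final value or to the change, so each reading is paired with the matching comparison. n per group is 27.98 × (1 − saving), rounded up, to be compared with 28. The 95% CI half-width at 29 per group is 1.96 × 3.0 × √(2/29) = 1.54 unadjusted, multiplied by √(1 − saving).

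| r (assumed) | Final values: saving | n | CI half-width | Changes: saving | n | CI half-width |
|---|---|---|---|---|---|---|
| 0.3 | 9% | 26 | 1.47 | 35% | 19 | 1.24 |
| 0.5 | 25% | 21 | 1.34 | 25% | 21 | 1.34 |
| 0.7 | 49% | 15 | 1.10 | 15% | 24 | 1.42 |
| 0.8 | 64% | 11 | 0.93 | 10% | 26 | 1.46 |

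The gain is positive in every row. It grows with r when final values are compared and shrinks with r when changes are compared.

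**4. Validity check.** Simulation of two arms of 29, normal data, SD 3.0, final values, 4,000 runs per setting, r = 0.5, 0.7 and 0.8. With no true difference, the rejection rate was 4.1% to 4.9% for the t-test, the Mann-Whitney test (standing in for a pairwise rank comparison) and the baseline-adjusted model. With a true difference of 1.8 and r = 0.7, power was 61%, 57% and 87% respectively. At the design difference of 2.6 and r = 0.7 it was 90%, 88% and 99%. These are single-comparison figures. They do not address multiplicity, the strata, or a test chosen after looking at normality.

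**The case against.** The strongest reply is that nothing is broken. The unadjusted design delivers its stated 90% power, and the error rate per comparison is controlled. That stands: this is a matter of precision and interpretability.

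A reader might infer that a large share of the precision is wasted. The documents do not support that as a general statement. It needs final values to be compared and r of about 0.5 or more. The protocol gives no r, and selection partly on VO2peak below 20 may narrow the baseline range and lower it. If changes are compared, which section 11(2) does not exclude, baseline is already used in part, and the saving is 10% to 25% of the variance for r from 0.8 to 0.5.

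Four further inferences should be held back:
- **That the strata are ready to use.** No stratification factor is named, so the gain from including them cannot be computed.
- **That the Kolmogorov-Smirnov test selects the primary test.** This is a reasonable guess, but the text does not say so.
- **That no pairwise comparison is planned, because ANOVA and Kruskal-Wallis on three groups are omnibus tests.** The sentence plainly intends pairwise comparisons. The wording is loose, and the procedure could sit in a statistical analysis plan.
- **That 29 per arm is the analysis number.** Section 11(1) carries values forward so that the number analysed matches the number at the start, which is close to 35 per arm. The percentage savings above do not depend on this; the half-widths do.

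**Conclusion.** The point holds as a recommendation on efficiency and reporting. Section 11(2) commits the trial to an unadjusted between-group test while the baseline value of every outcome is scheduled and allocation is stratified. The variance saving from baseline adjustment is 9% to 64% over r = 0.3 to 0.8 if final values are compared, and 35% to 10% over the same range if changes are compared. Both ranges rest on an assumed r and on equal SDs at baseline and follow-up. Separately, and with no assumption about r, the Kruskal-Wallis route yields no difference in ml/kg/min.

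It does not follow that the trial is underpowered or its tests invalid. At the design difference, one unadjusted comparison has the stated power, and the sample size need not change. The change should be made, but the trial does not fail without it.

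**What to change.** Replace the between-group sentence in section 11(2) with wording to this effect: week-12 VO2peak is analysed by a linear model with arm, baseline VO2peak and the stratification factors used in the randomisation; the adjusted moxibustion-sham and moxibustion-blank differences are reported with 95% confidence intervals. Week 12 is taken here because it is the end of treatment.

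Use the same model for the other continuous outcomes, each with its own baseline value, on the log scale where the metabolites need it. Keep Kruskal-Wallis as a sensitivity analysis, not as an alternative primary test. Name the stratification factors in section 3(2), since the model cannot be written without them.

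The cost is small: a one-sentence revision of the analysis section plus the factor names, with re-submission to the ethics committee under section 12(1) if it is made during the trial. Sample size, visits and data collection stay as they are. The change should be settled before outcome data are examined.
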